### Outcome measures

2.6

Assessments of clinical variables will be performed at baseline (1W) and weeks 2 (2W), 4 (4W), 6 (6W), and 8 (8W). Table 4 shows the assessment schedule.

**Table 4 T4:**
[figure not shown]
Schedule for the treatment and the outcome measurements.

The primary endpoint is the mean change in VAS score at 4W. VAS is one of the methods to grasp the patient's subjective pain scale, and the patient marks the pain on a 100-mm straight line. In general pain assessment, the left end of the line indicates no pain while the right end indicates the maximum pain imaginable. In this study, the severity of the symptoms will be indicated by a straight vertical line drawn on the scale for the knee pain felt within the last 48 hours, which will be used by the assessor for measurement with a ruler.^[29]^

The secondary endpoints include the mean change in VAS at 2W, 6W, and 8W, the mean change in the individual scores of three subscales (pain/stiffness/physical functioning) and the total score for the Korean Western Ontario and McMaster Universities Osteoarthritis Index (K-WOMAC) at 2W, 4W, 6W, and 8W, the mean change in EuroQol 5-Dimension 5-Level scores at 2W, 4W, 6W, and 8W, and the mean dose of rescue drug taken assessed at 2W, 4W, 6W, and 8W.

The K-WOMAC is a tool for measurement of pain in osteoarthritis patients and is one of the most widely used indicators of overall knee joint function. It can comprehensively evaluate knee joint pain, disability, and the limitations in certain functions. The K-WOMAC consists of 24 questions in total with three subscales, including 5 questions on pain, 2 questions on stiffness, and 17 questions on other physical functions of difficulties in performing related daily activities. This tool is a self-assessment tool completed by the patient that assesses the condition in the past 48 hours, and takes about 3 minutes to complete. Each question is answered on a 5-point Likert scale (0 = none, 1 = mild, 2 = moderate, 3 = severe, and 4 = extreme). The range of scores is 0 to 20 for pain, 0 to 8 for stiffness, and 0 to 68 for physical function. The sum of the scores for these scales is the total K-WOMAC score, which ranges from 0 to 96. High scores in the assessment indicate deterioration in symptoms, limited activities, and bad health.^[30,31]^

The EuroQol 5-Dimension 5-Level is a tool for assessing the quality of life that was newly created to improve the sensitivity and the ceiling effect of EuroQol 5-Dimension 3-Level (EQ-5D-3L). Subjects check off the most appropriate sentence for their health condition under 5 areas, including mobility, self-care, usual activities, pain/discomfort, and anxiety/depression. Each item checked off is indicated by a number from 1 to 5 (1 = no problems, 2 = slight problems, 3 = moderate problems, 4 = severe problems, and 5 = extreme problems), and the weighted combination of these 5 numbers is expressed as an index between 0 and 1, where 0 indicates death and 1 indicates full health.^[32]^

The rescue drug necessary for knee pain management will be provided to the subjects during the study period and the dose taken will be assessed. Evaluating the dosage of rescue drugs provides information on the analgesic effects of the intervention, as effective pain control in the intervention group will reduce the required dose of the rescue drug. The subjects will receive sufficient rescue drug and a dosing diary during the study period. Instructions will be given to fill out the dosing diary every day and to bring it as well as the remaining rescue drug at the time of visits, so as to check the dosage of rescue drug.^[33]^

### Adverse events

2.7

In this study, AEs refer to all undesirable medical findings that appear after the start of the clinical trial. The medical conditions and diseases that existed before the trial are considered as AEs only if they worsen after starting the treatment. Subjects will be instructed to voluntarily report AEs as they appear, and the investigator will perform AE assessments at every visit based on the results of vital signs, interviews, and other examinations. Regardless of the relationship to the intervention, all identified AEs will be recorded in the CRF. In cases serious adverse events (SAEs) occur during the study period, they will be reported to the Institutional Review Board (IRB) and the monitoring agent within 24 hours of awareness and the clinical trial for the corresponding intervention will be stopped. In addition, follow-up reports will be submitted with additional safety information until AEs terminate.

### Statistical analysis

2.8

Analysis is carried out using the program SAS Version 9.4 (SAS institute. Inc, Cary, NC). All statistical analyses are two-tailed test, and the significance level will be set to 5%. For missing values, multiple imputation is used.

The full analysis set and the per-protocol set will be used in the analysis of data obtained from the subjects. The full analysis set refers to minimizing subjects excluded from analysis and analyzing the set of subjects excluded only for justifiable reasons. The per-protocol set refers to the analysis of the subject group with no protocol violations who have completed at least 75% of the participation level (at least 3 TEA and at least 6 EA in the intervention group) and all measurements for endpoints indicated in the protocol.

Descriptive statistics are presented for the demographic characteristics and basic clinical data such as gender, age, medical history, and medication history by intervention group. For continuous variables, comparison by each group will be analyzed by an independent *t* test or Wilcoxon rank sum test after presenting the means and standard deviations, along with the 95% confidence intervals, if necessary. For categorical variables, analysis will be carried out using the Chi-squared test or Fisher Exact test after presenting the frequency and percentiles.

The primary efficacy endpoint is the mean change in VAS at week 4 compared to baseline, and will be analyzed using an analysis of covariance with each group as the fixed factor and the VAS before intervention and age as the covariates. If there is a clinical difference between groups in demographic and preintervention characteristics, it will be corrected by adding it as a covariate if needed. The analysis for secondary endpoints will be carried out using the same method as for the primary efficacy endpoints. In addition, to analyze the differences in measurements before and after the intervention within each group, a paired *t* test or Wilcoxon signed-rank test will be used for the primary and secondary efficacy endpoints. To test for the difference in trends by visit, repeated-measures analysis of variance will be performed. For multiple comparison correction, Dunnett procedure will be used.

Safety assessments will be mainly performed by analyzing the incidence of AEs and SAEs that are suspected to be related to the intervention by the investigator. AEs will be collected through symptom reports from subjects and observations by the investigator. The frequency of AEs related and unrelated to the intervention will be recorded and presented as descriptive statistics.

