**Table 1 T1:**
[figure not shown]
Inclusion and exclusion criteria.

Subjects voluntarily consent to participating in the clinical trial and sign the written consent form. A series of surveys and tests will be performed to determine eligibility, which include a demographic information survey, interview on medical history, questionnaire assessments, blood tests, electrocardiogram examinations, knee radiographic examinations, and urine human chorionic gonadotropin tests for women of childbearing potential. Once eligibility has been determined, the subjects will be notified of their availability to participate, and eligible subjects will be randomized to the (TEA + EA + Usual care) group and (Usual care only) group in a 1:1 ratio. The (TEA + EA + Usual care) group will receive TEA treatment once a week for 4 weeks for a total of 4 sessions and EA twice a week for a total of 8 sessions while continuing usual care. The (Usual care only) group will only receive usual care for 4 weeks. During the 8-week study period, there will be 3 visit assessments (weeks 2, 4, and 8) and 1 nonvisit assessment (week 6).

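### The per-protocol set requires every endpoint measurement, so missing week-6 or week-8 data removes patients from the per-protocol version of the week-4 primary comparison

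*Protocol article*

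**What the plan says.** Section 2.8 (Statistical analysis) sets three conditions for the per-protocol set:

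- no protocol violations;
- completion of "at least 75% of the participation level (at least 3 TEA and at least 6 EA in the intervention group");
- completion of "and all measurements for endpoints indicated in the protocol".

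The third condition is not limited to the endpoint or the time point being analysed, and the section defines no separate per-protocol set by endpoint.

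The same section states: "The primary efficacy endpoint is the mean change in VAS at week 4 compared to baseline". Section 2.6 (Outcome measures) continues past that time point: "The secondary endpoints include the mean change in VAS at 2W, 6W, and 8W", K-WOMAC at weeks 2, 4, 6 and 8, "the mean change in EuroQol 5-Dimension 5-Level scores at 2W, 4W, 6W, and 8W", and rescue-drug dose at the same four times. Section 2.2 describes three visits (weeks 2, 4 and 8) and "1 nonvisit assessment (week 6"). Sections 2.2 and 2.5.1 give a treatment period of 4 weeks.

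Section 2.8 also provides a full analysis set, meant to keep exclusions to a minimum, and multiple imputation for missing values. It uses both analysis sets without saying which one is primary.

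**The concern.** A per-protocol set is meant to show the treatment contrast among patients who followed the protocol up to the endpoint. Here membership also depends on what is recorded two and four weeks after both the primary time point and the end of treatment. Missing a week-6 contact or a week-8 visit says nothing about whether the patient received the assigned treatment or has a usable week-4 VAS.

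Two things are at stake. The first is loss of valid week-4 data from the per-protocol result of a small trial. The second is selection: sections 2.4 and 3 acknowledge that subjects are not blinded, so whether a patient returns after week 4 could depend on arm and on how the patient has fared. Conditioning a week-4 comparison on that return can distort it.

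The rule also bears differently on the two arms. The session counts attached to the 75% threshold are given for the intervention group only. In the usual-care arm, completeness of measurement is the only explicit completion requirement that the article spells out. Missing values at week 6 are plausible, because that assessment is not a visit while section 2.6 has the patient mark a VAS line that the assessor measures with a ruler.

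**Working it through.** **1. The plan's own figures.** Section 2.3 gives 14 evaluable patients per group and 20% dropout. 14 / (1 − 0.20) = 17.5, rounded up to 18 per group and 36 in total, as stated. The participation threshold is also consistent: 0.75 × 4 = 3 TEA sessions and 0.75 × 8 = 6 EA sessions.

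**2. What the 75% governs.** The bracket translates 75% into session counts and nothing else. The measurement condition follows it with its own quantifier, all, so the 75% does not soften it.

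**3. What "and all measurements for endpoints indicated in the protocol" covers.** VAS, K-WOMAC and EQ-5D-5L at baseline and four later times, plus rescue dose at four times: 3 × 5 + 4 = 19 instrument-occasions. After week 4 there are 4 measures × 2 times = 8. Missing any one of these 8 excludes a patient whose primary endpoint is complete.

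**4. Size of the loss due to weeks 6 and 8 alone.** The article gives no missingness rate, so the probability q of missing an assessment is assumed. With independent misses, the expected number per arm of 18 who have week-4 data but lack week 6 or week 8 is 18 × [(1 − q) − (1 − q)³].

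| q | With week-4 data | Also with weeks 6 and 8 | Removed per arm |
|---|---|---|---|
| 5% | 18 × 0.95 = 17.1 | 18 × 0.8574 = 15.4 | 1.7 |
| 10% | 18 × 0.90 = 16.2 | 18 × 0.729 = 13.1 | 3.1 |

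As a share of patients with week-4 data, this is 1 − 0.95² = 9.75% and 1 − 0.90² = 19%.

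**5. Sensitivity to the assumptions.**

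- *Clustered misses.* If everyone who misses week 6 also misses week 8, the loss per arm falls to 18 × 0.95 × 0.05 = 0.9 at 5% and 18 × 0.90 × 0.10 = 1.6 at 10%.
- *Scattered item-level gaps.* If each of the 8 later items is missed independently with probability 1% or 2%, retention is 0.99⁸ = 92% or 0.98⁸ = 85%. That is about 2.2 or 4.2 of the 28 planned evaluable patients lost.

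**6. After the change.** If membership for the primary endpoint required only baseline and week-4 VAS with the other two conditions, the loss caused by weeks 6 and 8 would be zero under every scenario.

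**The case against.** The strongest reply is that the consequence is contained. A reader might infer that these patients vanish from the primary comparison altogether. The article does not support that: nothing in section 2.8 removes them from the full analysis set, where exclusions need a justifiable reason and missing values are imputed. This stands, and it confines the point to the per-protocol result. It does not dispose of the point, because the article does not say that the per-protocol result is merely supportive.

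A reader might also put the loss higher by counting all four post-baseline assessments: 18 × (0.95 − 0.95⁴) = 2.4 per arm at 5%, and 18 × (0.90 − 0.90⁴) = 4.4 at 10%. Those figures include week 2, which precedes the primary endpoint, so they overstate what the later assessments do. Nor can missed diary days be added. Section 2.6 says "Instructions will be given to fill out the dosing diary every day", but it also has patients bring back unused drug to check the dose, and nowhere treats a blank day as a missing endpoint measurement.

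The selection argument shows a possibility only. Section 2.5.2 offers usual-care patients compensatory TEA after the trial ends, which could as easily keep them in follow-up as not. No direction or size of bias can be read from the document. The planned 14 per group was also set on feasibility grounds, so no stated power is lost.

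Three further defences carry less weight:

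- *A single completers' set keeps one population across endpoints and suits a classical repeated-measures analysis of variance.* That justifies such a subset for the by-visit analysis, but not for the week-4 comparison.
- *Analysis sets are often detailed in a full protocol or SAP that is not shown.* The article does not leave this open; it states the rule.
- *Multiple imputation would cover the gaps.* It can do so in the full analysis set. In the per-protocol set it has no endpoint values left to impute, since members have complete endpoint data by definition.

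**Conclusion.** The point holds for the per-protocol version of the primary comparison and no further. As written, section 2.8 excludes patients with adequate treatment and valid baseline and week-4 VAS on account of measurements due after the primary endpoint. That this can happen follows from the text alone.

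How often it would happen rests on assumed missingness: about 1.7 of 18 patients per arm at 5% per assessment and 3.1 at 10% under independence, and fewer if misses cluster in the same patients. Bias is possible because subjects are unblinded, but it is not demonstrated and its direction is unknown. It would go too far to conclude that the primary result is biased, or that the data are lost to the trial. This is a cheap improvement worth making in a non-powered pilot; it does not threaten the trial's main analysis.

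**What to change.** In section 2.8, replace the single measurement condition with endpoint-specific ones:

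- **Primary endpoint:** the stated treatment-adherence rule, absence of protocol violations, and valid baseline and week-4 VAS.
- **Each secondary endpoint and time point:** the same adherence and violation conditions, with baseline (where a change is analysed) and the measurement being analysed.
- **By-visit repeated-measures analysis:** if complete visits are needed, keep the all-measurements subset for this analysis only.

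The change takes one or two sentences and uses data already being collected. Its cost is that the per-protocol n will differ between endpoints and time points, so each table must report it.

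### Paired before-after tests within each arm are planned alongside a sound between-group ANCOVA; they cannot show a treatment effect and should become description only, and the trend analysis should be pinned down

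*Protocol article*

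**What the plan says.** The Objective section (2.1) sets a comparison of week-4 VAS change between the two groups. Section 2.8 follows this for the primary endpoint, which "will be analyzed using an analysis of covariance with each group as the fixed factor and the VAS before intervention and age as the covariates". It extends the approach: "The analysis for secondary endpoints will be carried out using the same method as for the primary efficacy endpoints".

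Two further analyses follow. The first is introduced by "In addition, to analyze the differences in measurements before and after the intervention within each group", and the method is that "a paired *t* test or Wilcoxon signed-rank test will be used for the primary and secondary efficacy endpoints". The second is: "To test for the difference in trends by visit, repeated-measures analysis of variance will be performed".

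Two general statements in the same section apply to all of this: "All statistical analyses are two-tailed test, and the significance level will be set to 5" per cent, and "For missing values, multiple imputation is used". The paired tests are not labelled descriptive. For the ANOVA, the section names no group-by-visit term, covariance structure or sphericity correction, and does not say how it is combined with the imputation.

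**The concern.** A paired test in one arm asks whether that arm changed from baseline. It makes no use of the randomised control. Natural course, regression to the mean, usual care, rescue medication and expectation all contribute to the change. The Discussion accepts that placebo and expectation effects are possible because neither practitioners nor subjects are blinded, and patients enter because of persisting pain. Improvement in both arms is therefore plausible without any effect of TEA and EA.

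The risk is a report that the TEA+EA arm improved significantly while usual care did not, read as efficacy. The risk is greater in a small trial, because a non-significant ANCOVA can easily stand beside a significant paired test.

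The ANOVA raises a smaller issue. Outcomes are measured at baseline and weeks 2, 4, 6 and 8. Neighbouring visits usually correlate more strongly than distant ones, and the plain univariate F test for group by visit is then too liberal. As named, the ANOVA also lacks the baseline and age adjustment of the primary analysis.

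**Working it through.** **The plan's own figure.** Section 2.3 gives 14 per group and 20% dropout: 14 / (1 − 0.20) = 17.5, rounded up to 18 per group and 36 in total. This reproduces. No effect size, SD or power is stated, so those inputs below are assumptions shown over a range.

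**Within-arm tests when there is no treatment effect.** Let both arms have the same true mean change d, in units of the SD of the change. The power of a two-sided 5% paired t test in one arm is p = P(|T| > t(0.975, n − 1)), where T is noncentral t with n − 1 degrees of freedom and noncentrality d√n. The arms are independent, so the chance that TEA+EA is significant and usual care is not is p(1 − p). For n = 14 and d = 0.5, the noncentrality is 0.5 × √14 = 1.87, p = 0.410, and 0.410 × 0.590 = 0.242.

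| d (assumed) | n = 14: p | n = 14: p(1 − p) | n = 18: p | n = 18: p(1 − p) |
|---|---|---|---|---|
| 0.3 | 18.0% | 14.8% | 22.5% | 17.4% |
| 0.5 | 41.0% | 24.2% | 51.6% | 25.0% |
| 0.75 | 73.7% | 19.4% | 85.0% | 12.7% |
| 1.0 | 93.2% | 6.3% | 97.9% | 2.1% |

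A valid two-sided 5% comparison of the arms would wrongly favour TEA+EA 2.5% of the time. The product p(1 − p) peaks at 25% when p = 0.5 and falls once improvement is large enough for both arms to be significant nearly always.

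**How often the pattern could arise.** VAS, four K-WOMAC scores and EQ-5D-5L at four visits give (1 + 4 + 1) × 4 = 24 endpoint-visits, so up to 24 × 2 = 48 paired tests without rescue dose. They are correlated, so the table applies to each pair and should not be multiplied up.

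**Power of the randomised comparison.** By the normal approximation, without covariates, 14 per arm gives 26% power at a standardised difference of 0.5 and 56% at 0.8.

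**Repeated-measures ANOVA, if run as the univariate test.** Type I error of the group-by-visit F test at nominal 5%, with two arms, five times and 20,000 simulated null trials per setting (simulation error about √(0.05 × 0.95 / 20,000) = 0.15 percentage points):

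| Correlation (assumed) | n = 14: uncorrected | n = 14: Greenhouse-Geisser | n = 18: uncorrected | n = 18: Greenhouse-Geisser |
|---|---|---|---|---|
| Compound symmetry 0.5 | 5.1% | 4.1% | 5.1% | 4.4% |
| AR(1) 0.5 | 6.0% | 4.3% | 5.9% | 4.4% |
| AR(1) 0.7 | 6.8% | 4.4% | 6.9% | 4.6% |
| AR(1) 0.9 | 8.2% | 5.0% | 7.8% | 4.9% |
| AR(1) 0.7, SD doubling over visits | 7.7% | 4.7% | 7.6% | 4.8% |

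The mixed model was not simulated, because the protocol gives no SD, correlation or pattern of missing visits.

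**The case against.** The strongest reply is that the main analysis is sound. Primary and secondary endpoints are both compared between groups by ANCOVA. The paired tests come as an addition with a stated within-group purpose, and nothing says that they will carry an efficacy claim. This stands: a reader might infer that efficacy rests on the paired tests, and the text does not support that. What remains is that they are formal 5% tests on the efficacy endpoints with no descriptive label, and they do not address the trial's objective.

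A reader might also take the ANOVA to be the classical uncorrected form that discards anyone with a missing visit. The text supports neither part. It gives only the general name, and SAS can fit a corrected or covariance-structured version. Multiple imputation is stated in the same section, and the per-protocol set requires all endpoint measurements. A condensed article may leave the covariance structure to a fuller document, so that silence alone would not be a finding. The 6 to 8% is therefore conditional on the uncorrected test being used. How the ANOVA and the imputation fit together is still unstated.

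A figure in millimetres for regression to the mean is also tempting. The text at hand gives no entry VAS, SD or retest correlation, so any single value would be guesswork. Regression to the mean acts in both arms, and the planned ANCOVA deals with it.

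Finally, this is a pilot not sized by calculation, and its Discussion admits the small sample and lack of blinding. That limits the consequences but does not make a within-arm p-value informative about treatment.

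**Conclusion.** The point holds for the within-arm tests. With no treatment effect and equal improvement in both arms, the pattern of significance in TEA+EA alone has a chance of about 6 to 24% per endpoint-visit at 14 per arm and 2 to 25% at 18. This assumes a standardised change of 0.3 to 1.0, equal in the two arms. The tests add a route to a misleading claim and no evidence on the objective.

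The ANOVA point is secondary and conditional. If the test is uncorrected and univariate, type I error is about 6 to 8% under AR(1) correlation of 0.5 to 0.9, 5% under compound symmetry, and 4 to 5% with a Greenhouse-Geisser correction. It would go too far to conclude that only a mixed model is acceptable; a corrected ANOVA on imputed data is valid too. Neither point undermines the primary ANCOVA. The change is worth making because it is cheap.

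**What to change.** 1. Delete the paired t and Wilcoxon signed-rank tests. Show mean change within each arm with its 95% confidence interval, labelled as description, and state that every efficacy conclusion rests on the difference between arms.
2. Preferably replace the repeated-measures ANOVA with a mixed model for repeated measures on change at weeks 2, 4, 6 and 8. Include arm, visit, arm-by-visit, the outcome's own baseline and age, with unstructured covariance, a named simpler fallback and Kenward-Roger degrees of freedom. Report the arm difference with a 95% confidence interval at each visit.
3. If ANOVA is kept, name the group-by-visit test and the sphericity correction, and run it on the imputed data with a stated pooling method.
4. Either way, say how the longitudinal analysis relates to the multiple imputation: for example, whether the mixed model uses the observed data directly while imputation serves the ANCOVA, or is fitted to the imputed data sets and pooled.
5. For rescue dose, for which the text describes no baseline value, model the dose itself without a baseline term.

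The cost is a few lines in SAS 9.4, which the protocol already names. Sample size, visits and data collection do not change. The one downside is that the unstructured covariance may not converge with so few patients, which is why the fallback should be named in advance.

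### The main safety measure counts events attributed to an intervention that only one arm receives; an all-cause summary by arm, with the contrast taken at the shared visits, would be a fairer lead.

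*Protocol article*

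**What the plan says.** Safety is the second of the two objectives in Section 2.1 (Objective). Section 2.8 (Statistical analysis) says safety assessment will be "mainly performed by analyzing the incidence of AEs and SAEs that are suspected to be related to the intervention by the investigator". The same paragraph adds: "The frequency of AEs related and unrelated to the intervention will be recorded and presented as descriptive statistics".

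Section 2.7 (Adverse events) sets out collection. "Regardless of the relationship to the intervention, all identified AEs will be recorded in the CRF". There are two routes. One is spontaneous: "Subjects will be instructed to voluntarily report AEs as they appear". The other is direct enquiry by study staff: "the investigator will perform AE assessments at every visit based on the results of vital signs, interviews, and other examinations". A condition present before the trial counts as an AE if it worsens after treatment starts.

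Section 2.2 (Study design) gives the contacts. The TEA+EA arm has 4 weekly TEA sessions and "EA twice a week for a total of 8 sessions"; the usual-care arm has no study treatment sessions. For the study as a whole, "there will be 3 visit assessments (weeks 2, 4, and 8") plus a week 6 assessment that is not a visit.

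Section 2.4 (Randomization and blinding) accepts that practitioners and subjects can hardly be blinded. It describes blinded assessors for the efficacy assessments. It does not mention AE assessment or causality.

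**The concern.** The trial has a randomized control arm, but the safety measure it puts first cannot use that arm. An event related to TEA or EA is zero or undefined in subjects who receive neither. The measure also passes through a judgement that is hard to make without knowing whether the subject was needled.

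The events most exposed to this filter are those for which a control arm is most useful. A flare of knee pain or swelling is a recordable AE in both arms under Section 2.7. If it is judged to be due to the disease, it drops out of the main measure, and the reader must look for it in the unrelated part of a descriptive table.

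The all-cause count may have a different problem. If AEs are sought at treatment sessions as well as at assessment visits, minor and transient events have more chances to be found in the TEA+EA arm. The attribution filter can understate harm and unequal questioning can overstate it, so neither planned summary gives a clean contrast between the arms.

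**Working it through.** **Arm size.** Section 2.3 plans 14 evaluable subjects per group and 20% dropout: 14 / (1 − 0.20) = 17.5, rounded up to 18 per group and 36 in total. This reproduces the plan's figure. The article gives no AE rate, so nothing else in its safety plan can be recomputed.

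**Related events.** With usual care fixed at 0 of 18, Fisher's exact two-sided p is 0.10 for 4 of 18 against 0 of 18, and 0.0455 for 5 of 18 against 0 of 18. Five attributed events would therefore cross the 5% level of Section 2.8, although the control count could not have been anything but zero. Section 2.8 names no test for AEs; the calculation shows only that such a test would carry no information.

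**Number of AE enquiries per subject.** Inputs from Section 2.2: 4 TEA sessions, 8 EA sessions, assessment visits at weeks 2, 4 and 8, and a nonvisit assessment at week 6. The article text does not say which contacts coincide, and the schedule (Table 4) is not shown.

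| Counting rule | TEA+EA | Usual care | Ratio |
|---|---|---|---|
| TEA given at EA sessions, weeks 2 and 4 assessed at sessions, plus week 8 | 8 + 1 = 9 | 3 | 3.0 |
| As above, first session at baseline, post-baseline contacts only | 8 | 3 | 2.67 |
| As above, baseline counted in both arms | 9 | 4 | 2.25 |
| First rule, with the week 6 contact counted | 10 | 4 | 2.5 |
| Assessments separate from the 8 sessions | 8 + 3 = 11 | 3 | 3.67 |
| First rule, first 4 weeks only | 8 | 2 | 4.0 |
| TEA, EA and assessments all separate | 4 + 8 + 3 = 15 | 3 | 5.0 |
| Formal assessment visits only | 3 | 3 | 1.0 |

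**What unequal enquiry could do.** Suppose each enquiry finds an otherwise unreported minor event with probability q, independently and equally in both arms. The proportion with at least one AE is 1 − (1 − q)^k, where k is the number of enquiries. With k = 9 and k = 3:

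- q = 0.05: 1 − 0.95^9 = 37% against 1 − 0.95^3 = 14% (6.7 against 2.6 of 18; ratio 2.59)
- q = 0.10: 61% against 27% (11.0 against 4.9 of 18; ratio 2.26)
- q = 0.20: 87% against 49% (15.6 against 8.8 of 18; ratio 1.77)

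The values of q are assumptions; the article supplies none. At the 1:1 count the two proportions are equal.

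**A zero count.** For 0 events in 18 subjects the exact two-sided 95% upper limit is 1 − 0.025^(1/18) = 18.5%.

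**The case against.** The best defence is that the article says *mainly*, not *only*. All AEs are recorded, and related and unrelated frequencies are both presented, so an event judged unrelated leaves the leading measure but not the report. A reader might infer that the plan ignores unrelated events; Section 2.8 shows that it does not.

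The second objective is also worded differently from the first. The first compares the two groups; the second examines AEs after the procedure. A reader might infer that a promised between-arm safety comparison has been spoiled, but none was promised. For a procedure in a small pilot, leading with suspected procedure-related events is a common choice.

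Two further inferences are tempting. One is that an unblinded investigator judges causality. The article does not say who judges it or whether that person knows the arm; it only fails to describe blinding for this task. The other is that AEs are sought three times as often in the TEA+EA arm. Section 2.2 uses *visit* for the assessments at weeks 2, 4 and 8, so on a narrow reading the frequency is equal.

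The detection model is also crude. A later interview can recover events since the previous one, and both arms are told to report AEs as they appear, so the extra contacts would yield less than the model assumes.

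All of this stands and limits the claim. It does not remove two facts: the measure placed first cannot be compared between arms, and the listing that could be compared is secondary and split by the same attribution.

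**Conclusion.** The point holds in a limited form. Section 2.8 leads with a measure that has no usable comparator and depends on a causality judgement for which no blinding is described. That follows from the text and needs no assumption.

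Uneven questioning is conditional. If treatment sessions count as visits, the ratio is about 3 (plausible counts 2.25 to 5.0); if only formal assessment visits count, it is 1.0. The 37% against 14% illustrates a mechanism under an assumed independent 5% yield per enquiry (61% against 27% at 10%). It is not a forecast.

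The 18.5% upper limit might be read as a cost of the attribution rule. It is not: it follows from 18 subjects and would be the same under any rule.

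The documents do not support saying that the trial can yield no fair safety comparison. Both arms share the visits at weeks 2, 4 and 8 and all AEs are recorded, so a fairer one is available; it is just not the planned main result. This is a cheap improvement rather than a fatal flaw.

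**What to change.** In Section 2.8, make the main safety summary the number of subjects with any AE, and with any serious AE, in each arm regardless of attribution, with exact 95% confidence intervals and the risk difference.

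Base the between-arm contrast on AEs elicited at the shared visits: weeks 2, 4 and 8, and week 6 only if AEs are asked about at that nonvisit contact. Ask the same question of both arms, covering the time since the previous shared visit. An event reported then should count even if a treatment session had already recorded it; otherwise the TEA+EA arm would be undercounted.

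Report procedure-related events, and events found only at treatment sessions, separately for the TEA+EA arm. State who judges causality, whether that person knows the allocation, and whether the AE assessment in Section 2.7 applies to treatment sessions.

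The cost is a change of analysis wording and a source flag on the AE form. Section 4 (Trial status) says recruitment has begun, so AE collection dates may have to stand in for the flag in subjects already enrolled. Dates alone cannot show whether an event first noted at a session would have been reported at the next shared visit. The contrast will rest on slightly fewer events, but the full listing loses nothing.
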